## Abstract

**Background:**

Targeted analgesic dietary interventions are a promising strategy for alleviating pain and improving quality of life in patients with persistent pain syndromes, such as chronic daily headache (CDH). High intakes of the omega-6 (n-6) polyunsaturated fatty acids (PUFAs), linoleic acid (LA) and arachidonic acid (AA) may promote physical pain by increasing the abundance, and subsequent metabolism, of LA and AA in immune and nervous system tissues. Here we describe methodology for an ongoing randomized clinical trial comparing the metabolic and clinical effects of a low n-6, average n-3 PUFA diet, to the effects of a low n-6 plus high n-3 PUFA diet, in patients with CDH. Our primary aim is to determine if: A) both diets reduce n-6 PUFAs in plasma and erythrocyte lipid pools, compared to baseline; and B) the low n-6 plus high n-3 diet produces a greater decline in n-6 PUFAs, compared to the low n-6 diet alone. Secondary clinical outcomes include headache-specific quality-of-life, and headache frequency and intensity.

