### Statistical Analysis

#### Overview

This study is a 2-arm intervention trial with a baseline measurement and with repeated measures of the outcome variable over time. The primary outcome variable is %n-6 in HUFA after dietary interventions. To correct for violations of the underlying assumptions of regression (e.g., normality, variance homogeneity), we plan to use a transformed value of the proportions as our dependent variable (angular, logit, or power transformation). We plan to invoke intent-to-treat analysis in dealing with missing data.

#### Analysis of Aim 1

In Aim 1, we will assess the extent of lowering %n-6 in HUFA after 12 weeks of targeted dietary interventions. All participants contribute specimens at randomization (week 6), and at weeks 10, 14 and 18. As a first step, we will test the equality of the transformed mean proportions after 12 weeks of the intervention with a t-test and will use the transformed proportions in a regression model to compare the treatment effects adjusting for covariates, including the baseline proportion and other variables that may influence the accumulation and turnover of LA in adipose tissue, such as age, sex, and baseline BMI.

#### Analysis of Aim 2

To test Aim 2, we will make use of the repeated measures of the outcome variable measured at 6, 10, 14, and 18 weeks to compare the rate of reduction in the %n-6 in HUFA over time in the 2 groups. Because the measurements within each person over time are correlated, we will use a hierarchical linear model with transformed proportions as the outcome variable. The first-level model specifies the outcome as a linear function of time. In the second level, the slope and intercept will be a linear function of the treatment variable. The random effects will represent the within- and between-group variances. The regression coefficients of the time-by-treatment terms are of interest here. If the regression coefficients of the interactions are not statistically significant from zero, we will conclude that the rate of change in the outcome variable over time is the same in both groups.

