#### Power calculations

Assuming that the %n-6 in HUFA will be on average 0.8, 0.5 and 0.3 at the end of the 12 weeks (as predicted by Lands empirical equation [31] and the nutrient intake targets) and a common standard deviation set at the maximum value of 0.5, we determined that, to achieve 80% power, we need 32 individuals per each arm. Repeated measures power-analysis procedures indicate that we will have adequate power (close to 80%) to test the time interaction effect with 32 persons measured over 4 time points (Aim 2).

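### Aim 2 reads a non-significant time-by-treatment term as proof that the two diets have the same rate of change

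*Protocol article*

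**What the plan says.** In Statistical Analysis, Analysis of Aim 2, the article plans a hierarchical linear model on the transformed proportions at study weeks 6, 10, 14 and 18, with slope and intercept depending on treatment. It names the estimand: "The regression coefficients of the time-by-treatment terms are of interest here". It then fixes how a null result will be read. The condition is "If the regression coefficients of the interactions are not statistically significant from zero", and the consequence is "we will conclude that the rate of change in the outcome variable over time is the same in both groups".

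The hypothesis behind this is one of difference. The Abstract asks whether "the low n-6 plus high n-3 diet produces a greater decline in n-6 PUFAs, compared to the low n-6 diet alone".

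On precision, Power calculations says that "we will have adequate power (close to 80%) to test the time interaction effect with 32 persons measured over 4 time points". The article gives no margin for similarity of slopes and no criterion based on the confidence interval, and no other section softens the Aim 2 sentence.

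**The concern.** A test of zero interaction can give evidence that the slopes differ. It cannot, by failing, give evidence that they are equal, because a non-significant result also arises when the difference is real but imprecisely estimated. The article treats the two situations alike and commits the investigators to the stronger statement.

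This is a stated inference rule, so it is not a matter of detail that the article could leave to a fuller protocol or SAP. Whether adding n-3 to a low n-6 diet changes the metabolic response is also one of the open questions in the Discussion, and the trial is meant to prepare a larger one. Followed literally, the rule would turn an inconclusive Aim 2 result into a positive finding that the added n-3 made no difference to the rate of change.

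**Working it through.** **1. The logic.** The rule has two outcomes: significant (rates differ) and non-significant (rates the same). There is no third outcome for an estimate too imprecise to decide. The fault lies there and does not depend on any number below.

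**2. The plan's own power figure.** The article gives close to 80% for the interaction, but states neither the slope difference nor the within-person correlation, so the figure cannot be reproduced. A range can be shown.

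- Inputs from Power calculations: SD 0.5; 32 per arm; three assumed means (0.8, 0.5, 0.3) for two arms, so the between-diet difference Δ could be 0.2 or 0.3.
- Assumptions made here: compound symmetry with correlation ρ; equal baselines; untransformed scale; two-sided 5%.
- Time scaled to 0, 1/3, 2/3, 1 gives Sxx = 0.25 + 0.0278 + 0.0278 + 0.25 = 0.556.
- SE of the slope difference = √[2 × 0.25(1 − ρ) / (0.556 × 32)]; power ≈ Φ(Δ/SE − 1.96).

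| ρ | power, Δ = 0.2 | power, Δ = 0.3 |
|---|---|---|
| 0 | 0.22 | 0.43 |
| 0.5 | 0.39 | 0.72 |
| 0.7 | 0.59 | 0.90 |
| 0.8 | 0.76 | 0.98 |
| 0.9 | 0.97 | 1.00 |

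Exactly 80% requires 1 − ρ = (Δ/2.802)² × 16 × 0.556/0.25. That gives ρ ≈ 0.82 for Δ = 0.2 and ρ ≈ 0.59 for Δ = 0.3. The stated power is therefore attainable, but only under inputs that the article does not give.

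**3. What the rule does if 80% is taken at face value.** With a two-sided 5% test, 80% power means that the planned difference equals (1.960 + 0.842) = 2.802 standard errors. If the true difference is a fraction f of it,

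P(non-significant) = Φ(1.960 − 2.802f) − Φ(−1.960 − 2.802f).

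- f = 1: Φ(−0.842) = 0.20
- f = 0.75: Φ(−0.141) = 0.44
- f = 0.5: Φ(0.559) − Φ(−3.361) = 0.71
- f = 0.25: Φ(1.260) − Φ(−2.660) = 0.89

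These are the probabilities that the rule declares the rates the same although they are not.

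**4. What the interval would show.** The 95% CI half-width is 1.960/2.802 = 0.70 of the planned difference. An estimate at half the planned difference would be non-significant, with an interval from −0.20 to 1.20 times that difference. Such a result is compatible both with no effect and with more than the planned effect, yet the rule would report it as sameness.

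**The case against.** **The sentence affects only the reading of a null.** This stands. It changes no estimate, test, error rate or sample size, and a significant interaction is interpreted correctly. Nor does the between-diet question rest on Aim 2 alone: Aim 1 compares the diets after 12 weeks of intervention by t-test and baseline-adjusted regression, with no such rule. A reader might infer that the trial's main conclusion is compromised; the document does not support that.

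**The percentages are not specific to this trial.** This also stands. The figures in step 3 hold for essentially any two-sided 5% test with 80% power, and the article does not state alpha or sidedness for Aim 2. The trial may be more precise than planned. Table 5 gives a week-12 CI of 60.3 to 69.0 with n = 18, hence SD ≈ (4.35/2.11) × √18 ≈ 8.7 points with both diets pooled, against 50 points assumed. In a rough endpoint comparison with that SD and 32 per arm (untransformed, two-sided 5%, not a slope analysis), a 10-point difference would be missed less than 1% of the time, 7.5 points about 8% and 5 points about 39%. The risk shrinks for large differences and remains for moderate ones.

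**Linear time.** A reader might go further and object that "The first-level model specifies the outcome as a linear function of time" while the Table 5 means fall by 5.9, 3.0 and 2.7 points over successive four-week intervals. Those means are pooled over diets, untransformed and from 20 participants, so they say nothing about a difference in curve shape between arms. A linear time-by-treatment contrast remains an interpretable summary. Categorical time is a modelling preference, unconnected with how a null is read.

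**An equivalence margin.** A reader might also infer that a margin must be set. The hypothesis is one of difference, so none is required. Nor would one help much at 80% power. With a half-width of 0.70 of the planned difference, a rule that the whole 95% CI lie inside the margin could practically never be met for a margin below that. With the margin at the entire planned difference, it would be met in only 2Φ(2.802 − 1.960) − 1 = 60% of trials in which the diets were identical.

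**Conclusion.** The point holds as an error in a stated inference rule, of moderate severity. Non-significance of the Aim 2 interaction does not establish equal rates of change, and nothing in the article supplies a criterion that would.

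The size is illustrative: about 1 in 5 for a true difference of the planned size and about 7 in 10 for half of it. Both rest on accepting the stated power of close to 80% and on an assumed two-sided 5% level. They should not be quoted as this trial's operating characteristics, because the Aim 2 power cannot be reproduced from the article and Table 5 suggests a much smaller SD than planned. The logical fault stands whatever the true power is.

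**What to change.** Replace the last sentence of Analysis of Aim 2 with:

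> The between-diet difference in rate of change will be reported with its 95% CI; a non-significant result will be described as no difference demonstrated, not as equal rates.

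The cost is one sentence of wording. It needs no extra participants, visits or analyses, since the fitted model already yields the interval. The article reports that investigators other than the dietitian are still masked, so the change can be made before any between-diet result is known.

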#### Secondary Laboratory Aims

The study will explore multiple secondary aims. We will examine the metabolic impact of dietary interventions by examining the association between the plasma concentrations of n-6 AA-derived mediators and %n-6 in HUFA. We will employ a mixed model with repeated measurements of mediators as the outcome and with %n-6 in HUFA (transformed), time, and time by %n-6 in HUFA, to formally test the association between the two variables and the time trends.

We plan to analyze the impact of the dietary interventions on inflammatory gene expression. To estimate changes, we will analyze log fold-change as a continuous response. The hypothesis of no change in mean response will be tested at the 0.05/80 level, using a paired t-test, for each of the 84 genes correcting for multiple comparisons.

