#### Secondary Clinical Aims

We will also examine clinical data, including the diary data and the HIT-6 score. The 24-hour daily diary, successfully used in a previous UNC study, collects hourly headache experience for 18 weeks [34]. To examine the role of headache frequency, we will use the diary data to construct summary measures of headache experience for each day, including the number of headache hours in a day and the number of hours with moderate-severe headaches. With the repeated measurements of headache hours per day as the outcome variable, we will construct random-effects Poisson regression models with treatment as the exposure, and age and sex as covariates, to examine the association between the diets, blood fatty acids and their derivatives, and headache.

To test the effects on quality-of-life, we will construct a regression equation with the final HIT-6 score as the outcome variable, the treatment group as the exposure variable and the baseline HIT score as the control variable. We will also test a limited number of interaction effects to see whether the treatment effects vary by sub-groups (e.g., gender, age). In addition, controlling for the baseline score, we will examine the relationship between the post-intervention HIT score and post-intervention %n-6 in HUFA.

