1) Does the reduction of dietary n-6 LA and AA over a 12-week period decrease the abundance of LA and AA, and increase n-3 EPA and DHA, in human erythrocytes and plasma?

2) Does the reduction of dietary n-6 LA and AA decrease circulating levels of bioactive mediators derived from LA (e.g. endovanilloids) and AA (e.g. eicosanoids, endocannabinoids)?

3) Does the addition of n-3 ALA, EPA and DHA to low n-6 diets produce additional metabolic alterations?

4) Do low n-6, average n-3 diets and/or low n-6, high n-3 diets attenuate human physical pain? If so, are pain reductions correlated with alterations in tissue contents of specific fatty acids and/or their metabolic derivatives?

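### The only mediator model given for the impact of the diets has no treatment term, so it does not estimate the between-diet difference in mediators

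*Protocol article*

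**What the plan says.** The Secondary Laboratory Aims section of the protocol article states purpose and method in one sentence: "We will examine the metabolic impact of dietary interventions by examining the association between the plasma concentrations of n-6 AA-derived mediators" and %n-6 in HUFA. The model is a "mixed model with repeated measurements of mediators as the outcome and with %n-6 in HUFA (transformed), time, and time by %n-6 in HUFA", used "to formally test the association between the two variables and the time trends". Diet does not appear among the terms.

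Elsewhere the article names treatment when it wants a diet effect. In the Aim 2 model, "the slope and intercept will be a linear function of the treatment variable". The HIT-6 regression has "the treatment group as the exposure variable and the baseline HIT score as the control variable". Aim 1 compares treatment effects, and the diary model takes treatment as its exposure.

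Secondary Laboratory Outcomes lists lipid mediators derived from AA, EPA and DHA. Among the open questions in the Discussion is: "Does the addition of n-3 ALA, EPA and DHA to low n-6 diets produce additional metabolic alterations"?

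**The concern.** The stated target is what the diets do to mediators. The stated method relates mediators to %n-6 in HUFA, which is measured after randomisation and is itself an outcome of the diets. Randomisation protects a comparison of the two arms. It does not protect a regression of one post-randomisation variable on another.

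Two things are at stake. A clear association could be reported under the label of dietary impact when the diets do not differ on the mediator. Conversely, a real between-diet difference that is not reflected in %n-6 could be missed. In both cases the question about adding n-3 goes unanswered for mediators, even though the trial has randomised data to answer it.

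**Working it through.** **Reading the models side by side**

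| Outcome | Section | Treatment term named? |
|---|---|---|
| %n-6 in HUFA at week 18 | Analysis of Aim 1 | Yes |
| %n-6 in HUFA over time | Analysis of Aim 2 | Yes, on slope and intercept |
| Headache hours per day | Secondary Clinical Aims | Yes |
| Final HIT-6 | Secondary Clinical Aims | Yes |
| AA-derived mediators | Secondary Laboratory Aims | No |

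The diary paragraph mentions derivatives of blood fatty acids, but its outcome is headache hours. No section gives a model with a mediator as outcome and diet as exposure.

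**Illustration of size**

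The article gives no power or sample-size figure for the mediator analysis, so there is nothing of its own to reproduce. The simulation used these inputs.

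- From the article: 32 per arm (Power calculations); measurements at intervention weeks 0, 4, 8 and 12; pooled %n-6 in HUFA of 76.3 at baseline and 64.7 at week 12 (Table 5), a fall of 76.3 − 64.7 = 11.6 points.
- Assumed: the split of that fall by arm, 4 and 19.2, 8 and 15.2, or 11.6 in each (every pair averages 11.6); all variances; all mediator effects.

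With t = week/12:

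- Biomarker: x = 76.3 + u − (d + s)·[1 − (1 − t)^1.5] + e, where d is the arm's fall and the SDs are 3 (u), 3 (s) and 1.5 (e).
- Mediator: y = v − δ·arm·t + β·(x − 76.3) + ε, where v and ε each have SD 0.7. With β = 0 and no diet effect, the SD of y at a visit is √(0.49 + 0.49) = 0.99, so δ is close to SD units.

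Three random-intercept models were fitted by maximum likelihood at the 0.05 level, with z = logit(x/100):

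- (a) as written: z, t, z×t; joint test of the z terms.
- (b) as (a), plus arm and arm×t; same test.
- (c) t and arm×t; test of arm×t.

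Share of 150 runs rejecting:

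| Fall by arm | δ | β | (a) as written | (b) with arm terms | (c) arm×time |
|---|---|---|---|---|---|
| 4 / 19.2 | 0 | 0 | 8.7% | 7.3% | 4.0% |
| 4 / 19.2 | 0.5 | 0 | 48.0% | 9.3% | 70.7% |
| 4 / 19.2 | 1.0 | 0 | 97.3% | 7.3% | 100% |
| 8 / 15.2 | 0.5 | 0 | 25.3% | 5.3% | 70.0% |
| 8 / 15.2 | 1.0 | 0 | 78.0% | 8.0% | 100% |
| 11.6 / 11.6 | 0.5 | 0 | 6.0% | 7.3% | 71.3% |
| 11.6 / 11.6 | 0 | 0.1 | 100% | 100% | 4.0% |

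The Monte Carlo standard error is at most √(0.25/150) = 0.041, about 4 points.

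Rows 2 to 5: diet moves the mediator by a route other than %n-6, and model (a) reports a %n-6 association in 25% to 97% of runs. Row 6: the diets differ on the mediator but not on %n-6, and model (a) rejects about as often as it does with no effect (row 1). Row 7: the mediator follows %n-6 equally in both arms, so the diets do not differ, yet model (a) always rejects. Its result therefore says little, in either direction, about a between-diet difference.

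**The case against.** Several points on the other side stand.

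- **The word used is association.** A reader might infer that the plan reads the result as a causal effect of %n-6. The text does not say that. When diet moves both variables, a marginal association really exists, so the 25% to 97% are not false-positive rates for the hypothesis tested. They show only that the test does not isolate the diet contrast.
- **The biomarker is not a pure measure of n-6 lowering.** The long-chain n-3 fatty acids sit in the denominator of %n-6 in HUFA, and the Background describes EPA and DHA as competitors of AA. n-3 acting on AA-derived mediators while %n-6 falls is part of the hypothesised pathway. A reader might infer that the analysis would wrongly credit n-6 lowering with an n-3 effect; the documents do not support that.
- **Some scenarios are extreme.** The trial expects a greater n-6 decline with added n-3, so equal falls in both arms are a boundary case. The diet effect was also generated as linear in time, which favours model (c).
- **HIT-6.** A reader might extend the point to the sentence "we will examine the relationship between the post-intervention HIT score and post-intervention %n-6 in HUFA". That is an addition to a HIT-6 model that already has treatment as the exposure, so the randomised comparison is made there.
- **Adjusting the association for arm is debatable.** It removes the variation that randomisation created and leaves within-arm variation, such as adherence, which is observational.

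It can also be said that a condensed article need not print every model and that an unseen analysis plan may hold the comparison. That would answer a complaint about missing detail. Here the article states the purpose, chooses a model for it and lists the terms, and the two do not match.

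**Conclusion.** The point holds as a mismatch between target and method. The one mediator model in the article tests a biomarker association and does not estimate the randomised difference between diets. That follows from the listed terms and needs no simulation. It says nothing about comparisons that may be planned in a document not shown.

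The percentages are illustrative. They rest on the assumed arm split, variances and effects, and their width (25% to 97%) shows how strongly they depend on them. The 6% against 71% contrast belongs to the case where the arms do not separate on %n-6.

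The aim is secondary and exploratory. The primary outcome and the analyses of Aims 1 and 2 are unaffected. The change is worth making because it is simple and the question is one the trial itself poses.

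**What to change.** For each mediator, make the analysis of dietary impact a mixed model with treatment, time and treatment-by-time, adjusted for the week-6 mediator value. Report the week-18 between-diet difference with its 95% CI. The same model gives the change from baseline within each diet. Because both arms lower n-6, that change is not a randomised comparison and should be labelled so.

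Keep the %n-6 in HUFA association as a separate exploratory analysis, described as non-causal. A sensitivity version including treatment is optional.

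Reword the purpose sentence so that dietary impact refers to the first model and association to the second.

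The cost is one additional model per mediator. No further blood draws or assays are needed, because the planned model already uses repeated mediator measurements. The optional sensitivity version would estimate the association less precisely. The change should be fixed before the mediator data are analysed.

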#### Secondary Laboratory Outcomes

Secondary laboratory outcomes include individual n-6 and n-3 fatty acids in plasma and erythrocyte lipid pools, including n-6 linoleic acid (18:2n-6) and AA, as well as n-3 EPA and DHA. Lipid mediators derived from n-6 AA, EPA and DHA (e.g. eicosanoids, docosanoids), and mediators that may be indirectly influenced by n-6 and n-3 HUFA status (e.g. cytokines, pro-inflammatory enzymes, substance P), will be measured at study completion.

Changes in inflammatory gene expression in peripheral blood mononuclear cells (PBMCs) will be assessed in an additional pilot study. We will test: (1) the effects of the low n-6 diet compared to baseline dietary conditions (gene expression before the dietary intervention); (2) the effects of the low n-6 + high n-3 diet compared to baseline; and (3) the effects of the low n-6 versus the low n-6 + high n-3 diet compared to baseline. PBMCs are isolated from whole blood and RNA will be extracted utilizing Qiagen RNeasy Micro Kit (Valencia, CA). The RNA yield will be quantified with Nanodrop ND 1000 spectrophotometer (Nanodrop Technologies, Wilmington, DE), and integrity will be measured with an Agilent 2100 Bioanalyzer with RNA 6000 Nano chips (Santa Clara, CA). The expression of 84 key genes involved in the inflammatory response will be assessed using the Human Inflammatory Cytokines & Receptors RT² Profiler PCR Array (SA Biosciences, Frederick, MD).

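### The gene-expression analysis divides alpha by 80 for 84 genes, and the paired t-test it names cannot test the between-diet comparison

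*Protocol article*

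**What the plan says.** The protocol article describes the gene-expression work in two places.

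- **Secondary Laboratory Outcomes** gives the scope: "The expression of 84 key genes involved in the inflammatory response will be assessed". It then lists three comparisons to be tested. Comparisons (1) and (2) set each diet in turn against its own baseline. Comparison (3) is worded as "the effects of the low n-6 versus the low n-6 + high n-3 diet compared to baseline".
- **Secondary Laboratory Aims**, under Statistical Analysis, gives the method. Log fold-change is the continuous response, and the null of zero mean change "will be tested at the 0.05/80 level, using a paired t-test, for each of the 84 genes correcting for multiple comparisons". No other test is named for gene expression, and no reason is given for a divisor of 80.

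The Randomization section assigns each participant to one of the two diets for the whole 12-week intervention.

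**The concern.** The level and the gene count stand in the same sentence and disagree. A reader who applies the rule as written uses a slightly looser threshold than a Bonferroni correction for 84 genes allows, and a reader who notices the mismatch cannot tell which number was intended.

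The test is the more substantive part. Comparisons (1) and (2) ask whether expression changed within people on one diet. Comparison (3) asks whether the change differed between two groups of different people. The one test named answers only the first kind of question. Comparison (3) is also the only one of the three protected by randomization. The Limitations section concedes, for the clinical outcomes, that the lack of a usual-intake control group makes it hard to attribute changes to the diets themselves. Before-after changes in gene expression lack the same control group. The comparison with the firmest design basis is therefore the one for which the article states no usable method.

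**Working it through.** **Inputs**

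- Level per gene: 0.05/80 (Secondary Laboratory Aims).
- Genes tested: m = 84 (Secondary Laboratory Aims and Secondary Laboratory Outcomes agree).
- Comparisons: three (Secondary Laboratory Outcomes).
- Design: two parallel arms, one diet per participant (Randomization).

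**Step 1. Reproduce the stated level.** 0.05/80 = 0.000625. Multiplying back, 80 × 0.000625 = 0.0500, so the level is a Bonferroni correction for 80 tests.

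**Step 2. Apply it to 84 genes in one comparison.**

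- Bonferroni bound: 84 × 0.000625 = 0.0525.
- If the 84 tests were independent: 1 − (1 − 0.000625)^84 = 0.0512.

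Both exceed 0.05.

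**Step 3. See whether a standard variant for 84 tests gives 0.000625.**

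| Method | Level per gene |
|---|---|
| Stated | 0.000625 |
| Bonferroni, 0.05/84 | 0.000595 |
| Šidák, 1 − 0.95^(1/84) | 0.000610 |

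Neither does. The article mentions no removal of four genes before testing, and the sentence itself says that all 84 are tested.

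**Step 4. Match the test to the comparisons.** Let d be a participant's log fold-change from baseline, with mean δ₁ on the low n-6 diet and δ₂ on the low n-6 plus high n-3 diet.

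| Comparison | Null hypothesis | Suitable statistic |
|---|---|---|
| (1) | δ₁ = 0 | paired: d̄₁ / (s₁/√n₁) |
| (2) | δ₂ = 0 | paired: d̄₂ / (s₂/√n₂) |
| (3) | δ₁ − δ₂ = 0 | two-sample: (d̄₁ − d̄₂) / √(s₁²/n₁ + s₂²/n₂) |

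The paired statistic needs two measurements on the same person. For (1) and (2) these are the baseline and follow-up samples. For (3) they would have to be one person's response to each diet, and no participant receives both.

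Nor can the results of (1) and (2) stand in for (3). If δ₁ = δ₂ ≠ 0, both paired nulls are false while the null of (3) is true. The paired tests then tend to reject although the diets do not differ.

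**The case against.** The strongest reply has four parts.

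**The divisor barely matters.** The levels are 0.000625 and 0.000595, and only a gene with a p-value between them would be read differently. This stands as a statement of size. It does not remove the mismatch.

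**The article is silent on (3) rather than wrong.** The analysis sentence never says that the paired test will be used for the between-diet comparison, and a condensed article may leave that test to a fuller plan. This stands in part: one cannot say that the trial has no valid test for (3), only that none is stated here. But the sentence is offered as the analysis of the diets' impact on gene expression, it names one specific test, and that test fails for one of the three comparisons the article commits to. For other outcomes the article does state between-arm methods: the t-test and adjusted regression for Aim 1, and the HIT-6 regression with baseline score as control.

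**One family per comparison is defensible.** A reader might count 84 × 3 = 252 tests, obtain a bound of 252 × 0.000625 = 15.75% (14.6% under independence), and call 0.05/252 the right level. The document does not support this. The work is an exploratory pilot, and the three comparisons ask separate questions, so correcting across genes within each is acceptable. The 14.6% also assumes independence, which cannot hold, because the contrast in (3) is the difference between the changes in (1) and (2).

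**Misuse is not planned.** A reader might infer that the investigators would declare a diet difference because a gene is significant in one arm and not in the other. Nothing in the article says so, and its direct between-arm analyses elsewhere point the other way.

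**Conclusion.** The point holds in two limited parts.

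1. The per-gene level is wrong for the stated number of genes: the family-wise bound is 5.25% per comparison where 5% is intended. This assumes that all 84 genes are tested, as the text says, and that each comparison is its own family.
2. The only test named cannot address the between-diet comparison. This follows from the parallel-arm design and needs no numerical assumption. It reads comparison (3) as the difference between diets in change from baseline, which is the natural sense of its wording.

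The consequence is modest. The gene-expression work is a pilot within the secondary laboratory outcomes, and the primary outcome, Aims 1 and 2 and the sample size are untouched. A reader might also conclude that comparison (3) should be made the lead gene-expression analysis. The article ranks none of the three, so that would be a design choice and not a correction.

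**What to change.** In the Secondary Laboratory Aims section:

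- Replace 0.05/80 with 0.05/84 (= 0.000595), and state that the correction applies across genes within each comparison, each comparison being its own family in this exploratory pilot. If fewer than 84 genes are in fact to be tested, say which are excluded and why, and make the gene count and the divisor agree.
- Keep the paired t-test for comparisons (1) and (2), run separately within each diet.
- For comparison (3), name a two-sample (Welch) t-test of log fold-change, or a regression with diet as the exposure and baseline expression as a covariate. The second matches the approach the article already takes for Aim 1 and HIT-6.

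The cost is a few words. No new data or visits are needed, and the threshold tightens only from 0.000625 to 0.000595.
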